### Participants

2.2

Pregnant women with GDM are invited to participate if they are not more than 4 weeks after confirmation of GDM diagnosis (after a clinical visit when patient is informed of the diagnosis and prescribed with diet). GDM is diagnosed according to IADPSG (International Association of the Diabetes and Pregnancy Study Groups) criteria, i.e. fasting plasma glucose between 5.1 mmol/L and 6.9 mmol/L after the 6th week of gestation and/or 1-hour plasma glucose value after 75 g oral glucose tolerance test (OGTT) ≥ 10.0 mmol/L and/or 2-hour plasma glucose value between 8.5 mmol/L and 11.0 mmol/L at the 24-31^st^ week of gestation. According to Russian national guidelines, OGTT is performed between 24^th^-28^th^ week of gestation and in exceptional cases can be performed up to the 32^nd^ gestational week. The inclusion and exclusion criteria are listed in **Table 1**.

**Table 1 T1:** Inclusion and exclusion criteria.

Inclusion Criteria	Exclusion Criteria
• Women diagnosed with GDM according to IADPSG • Age >18 years • Gestational age >= 12 and < 32 weeks • No more than 4 weeks after confirmation of GDM diagnosis • Singleton pregnancy • The ability to navigate an app • Provided informed consent	• Preexisting diabetes of any type before the current pregnancy • Need for insulin therapy at the time of screening • Heart failure • Chronic kidney disease • History of bariatric surgery • Use of long-term systemic corticosteroids • Impaired mobility • Known fetal malformations • Concomitant participation in other clinical trials

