Secondary outcome measures are:1. Rate of patients requiring insulin therapy during pregnancy⚬ Rate of patients requiring insulin therapy (either basal or prandial)⚬ Rate of patients requiring prandial insulin therapy2. Capillary glucose values in the following time frames: within 2 weeks after randomization , at gestational weeks 35-37, and in the period from randomization up to delivery.⚬ Capillary fasting glucose values, mmol/L⚬ Capillary preprandial glucose values, mmol/L⚬ Capillary postprandial glucose values, mmol/L3. The proportion of women with glucose values within target in the following time frames: within 2 weeks after randomization, at gestational weeks 35-37, and in the period from randomization up to delivery.⚬ The proportion of women with fasting glucose values within the target⚬ The proportion of women with postprandial glucose values within the target4. Mean incremental area under the blood glucose curve 2 hours after meals (iAUC120) according to 7-day continuous glucose monitoring 1-2 weeks after randomization and at the 35-37^th^ GW.5. Hypoglycaemia⚬ Severe hypoglycaemia: requiring the assistance of another person to actively correct the level of glycaemia and neurological symptoms⚬ Documented symptomatic hypoglycaemia: event during which typical symptoms of hypoglycaemia are accompanied by a measured capillary glucose concentration <3.9 mmol/L⚬ Asymptomatic hypoglycaemia: event not accompanied by typical symptoms of hypoglycaemia but with a measured capillary glucose concentration <3.3 mmol/L6. Maternal metabolic parameters at 35-37^th^ GW (the level of HbA1c, Fasting insulin, Fasting glucose, HOMA-IR index, serum triglyceride levels).7. Gestational weight change by the time of delivery⚬ Gestational weight change during pregnancy, kg⚬ Gestational weight change between inclusion and delivery, kg8. Large (>90th percentile) for gestational age infant9. Small for gestational age (< 10th percentile) infant10. Birth weight, kg11. Birth weight ≥ 4000 g; ≥ 4500 g (yes/no)12. Neonatal hypoglycaemia defined as glucose levels <2,2 mmol/L in the first 4 hours of life or <2,5 mmol/L at 4–24 hours of age (yes/no) (17).13. Shoulder dystocia (yes/no)14. Birth injury, any of the following: plexus injury, clavicle, humeral, or skull fracture (yes/no)15. Preterm delivery (yes/no)16. Apgar score at 1 and 5 minutes from birth17. Low Apgar score: 5-min Apgar score < 7 (yes/no)18. Jaundice requiring phototherapy (yes/no)19. Neonatal respiratory distress syndrome (yes/no)20. Admission to neonatal intensive care unit during the three days following birth (yes/no)21. Umbilical cord blood C-peptide, ng/mL22. Cesarean delivery rate23. Induction of labor rate24. Need for operative vaginal delivery rate (forceps or vacuum-assisted vaginal delivery)25. Preeclampsia (blood pressure ≥ 140/90 mmHg on two measurements four hours apart and proteinuria of at least 300 mg/24 hours or 3+ or more on dipstick testing or proteinuria/creatinuria >30 in a random urine sample)26. Pregnancy-induced hypertension in women with no known hypertension before pregnancy (blood pressure ≥ 140/90 mmHg on two measurements four hours apart without proteinuria, and required anti-hypertensive therapy)27. The number of in-patient visits to endocrinologists in the time frame from randomization to delivery.28. Results of oral glucose tolerance test 3 months postpartum.29. Acceptance/satisfaction of 2 strategies at 35-36^th^ GW (Evaluation of the patient satisfaction with their treatment for GDM with a scale: give a score of 0 to 100: 0 not satisfied; 100 totally satisfied).30. Patient satisfaction evaluated through a questionnaire at 35-36^th^ GW.

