
We will use a 10-question questionnaire with multiple-choice questions, questions with numeric answers on a scale from 0 (fully unsatisfied) to 10 (fully satisfied), and open-ended questions.

The timetable of the planned visits and measurements is shown in **Table 2**.

**Table 2 T2:** Measurements timeline.

Measurements for both groups	Baseline	24^th^ GW*	35-36^th^ GW	Birth		Postpartum (3- 6 months)
Questionnaires (SF36, STAI, treatment attitude)	**x**		**x**			
Patient satisfaction questionnaire			**x**			
Physical examination (height, weight, blood pressure, oedema)	**x**	**x**	**x**			**X**
Medtronic CGM sensors	**x**		**x**			
Laboratory blood tests	**x**		**x**			
Cord blood samples and HUVECs				**x**		
Infant’s anthropometry, Apgar score, BG 1 hour after birth				**x**		
OGTT						**x**
Fecal, urine and saliva samples	**x**		**x**			
BG readings (glucometer)	**x**	**x**	**x**			
Measurements only for the intervention group:						
Data from DiaCompanion I app (BG readings, food tracker)	**x**	**x**	**x**			
Technology acceptance questionnaire			**x**			

*Visit at the 24^th^ GW will be scheduled for the participants included before the 20^th^ GW.

GW, gestational week; SF36, Short Form-36, STAI, State-Trait Anxiety Inventory, CGM, continuous glucose monitoring; BG, blood glucose; HUVECs, human umbilical vein endothelial cells; OGTT, oral glucose tolerance test.

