### Data analysis

2.9

The analyses will be performed on the intention-to-treat (ITT) basis, including all randomized patients. We will also perform a per-protocol analysis excluding women who did not use the DiaCompanion I app for at least 50% of expected meals to explore the efficacy of the system under optimal use.

Quantitative data will be assessed for normality using the Kolmogorov-Smirnov test. Log transformation could be used where appropriate. The data will be presented as mean and SD for normally distributed parameters and as median with quartiles for non-normally distributed characteristics. The distribution of binary or ordinary characteristics will be described as N (%).

The significance of differences in scale parameters (such as the percentage of postprandial capillary glucose values above target, the number of in-patient visits, etc.) between the control and intervention groups will be assessed by the Student’s t-test for normally distributed ones and Mann-Whitney test for ordinal and non-normally distributed characteristics. To compare the distribution of binary or ordinary characteristics (ex., rate of patients requiring insulin therapy during pregnancy, LGA, SGA, etc.) the χ2 criterion or Fisher’s exact test will be used. The Spearman correlation coefficient will be used to assess the relationship between two variables. We will use ANOVA repeated or nonparametric analogue for the analysis of repeated measurements (gestational weight change). The critical level of significance of the null statistical hypothesis will be assumed to be 0.05.

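### Gestational weight change is one value per woman but is assigned to repeated-measures ANOVA; a between-arm ANCOVA with gestational age at inclusion would be clearer and more precise

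*Protocol article*

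**What the plan says.** The Data analysis section (2.9) of the protocol article gives weight its own sentence: "We will use ANOVA repeated or nonparametric analogue for the analysis of repeated measurements (gestational weight change". It does not give the time points, the factors, the name of the nonparametric method or the handling of a missing visit. The same section promises an intention-to-treat analysis of all randomized women, and it assigns between-arm comparisons of scale parameters to the t-test or the Mann-Whitney test.

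Outcome 7 in Proposed outcome measurement (2.8) has two parts: "Gestational weight change during pregnancy, kg" and "Gestational weight change between inclusion and delivery, kg". Each is a single number per woman.

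In Table 2 the row "Physical examination (height, weight, blood pressure, oedema" is marked at baseline, the 24th week, weeks 35-36 and postpartum. The footnote limits one of these: "Visit at the 24^th^ GW will be scheduled for the participants included before the 20^th^ GW". Table 1 sets the entry window: "Gestational age >= 12 and < 32 weeks".

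**The concern.** The method named and the outcome defined do not match. Section 2.9 treats as a series of measurements something that section 2.8 defines as one change per woman, and the sentence on weight, unlike the sentence on scale parameters before it, does not mention a comparison of arms.

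The entry window makes this more than a matter of wording. A woman included at 12 weeks has far longer to gain weight before delivery than one included at 31 weeks. Repeated-measures ANOVA treats baseline as one common level and takes no account of this. The effect on the randomized comparison is lost precision, not bias, because gestational age at inclusion is fixed before randomization.

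The sentence is also loose enough to be carried out in two ways that would do more harm, one of which loses women by design and the other of which gives no treatment comparison.

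**Working it through.** The plan gives no sample size, power or effect for weight change, so there is no figure of its own to reproduce. The check works through the readings that the text allows.

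**1. Two time points (inclusion and delivery, as in the second part of outcome 7).** The 24-week visit plays no role and no woman is lost because of it. The arm-by-time F statistic then equals the square of the t statistic for the change score. A constructed data set confirmed this: F = 13.364 and t² = 13.364. The method is valid on this reading, but it is only an unadjusted change-score comparison.

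**2. What that comparison leaves in the error term.**
- Inputs: entry from 12 to under 32 weeks (Table 1). Assumed: delivery at 39 weeks, weight gain of 0.3 to 0.5 kg per week.
- Time from inclusion to delivery: 39 − 31 = 8 weeks to 39 − 12 = 27 weeks, a range of 19 weeks.
- Extreme spread in weight change: 19 × 0.3 = 5.7 kg to 19 × 0.5 = 9.5 kg.
- The range overstates the noise, so a standard deviation is the better measure. If entry were uniform over the window (assumed), SD = 19/√12 = 5.5 weeks, or 5.5 × 0.3 ≈ 1.6 kg to 5.5 × 0.5 ≈ 2.7 kg.

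The documents do not give the distribution of entry. If most women enter within a few weeks of the OGTT, the SD is smaller. The spread applies to change from inclusion; change over the whole pregnancy does not start at entry.

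**3. If the 24-week weight were a level in a complete-case ANOVA.** Only women included before 20 weeks have that visit, so all others would be missing by design. The share included early is not given. For assumed shares, the number kept is 216 × share:

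| Assumed share included before 20 weeks | Women kept of 216 |
|---|---|
| 10% | 22 |
| 20% | 43 |
| 30% | 65 |
| 50% | 108 |
| 70% | 151 |

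The loss would be selective. Participants (2.2) says that "OGTT is performed between 24^th^-28^th^ week of gestation", and in exceptional cases later, so every woman diagnosed by OGTT enters after 20 weeks and would be excluded.

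**4. If the analogue were the Friedman test.** Friedman ranks the visits within each woman and has no arm factor. In a simulation with 81 women per arm (108 less 25% dropout), 2,000 runs, and an assumed mean gain of 8 kg with SD of change about 4 kg, the rejection rates were:

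| Test | No arm effect | 2 kg arm effect |
|---|---|---|
| Friedman, three weights | 100% | 100% |
| t-test on change | 4.2% | 88.8% |
| Mann-Whitney on change | 3.5% | 87.3% |

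With neither a time effect nor an arm effect, Friedman rejected 4.3% of the time. It detects that pregnant women gain weight and says nothing about the app.

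**5. The end point of the change.** Outcome 7 runs to delivery, but the last weight in pregnancy marked in Table 2 is at 35-36 weeks. If that weight stood in for delivery weight, 3 to 4 weeks would be missed: 3 × 0.3 = 0.9 kg to 4 × 0.5 = 2.0 kg, on the same assumptions.

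**The case against.** The strongest reply is that the reading closest to the outcome definition is harmless. Outcome 7 names inclusion and delivery. With those two levels the ANOVA gives a valid test of the arms, equivalent to a t-test on change. Section 2.9 also offers the t-test or Mann-Whitney test for scale parameters in an open list, and weight change in kg is one. Time points, factors and the exact rank test are details that a condensed article may leave to an analysis plan. All of this stands.

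It also rules out several stronger conclusions that a reader might draw:

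- *That the plan discards women included from 20 weeks.* Nothing says that the 24-week weight enters this analysis, and the intention-to-treat statement points the other way. Even if it did happen, the selection would be on a characteristic fixed before randomization. It would cost precision and generalizability without in itself breaking the comparison.
- *That the arms will not be compared.* Friedman is not named, and rank methods for repeated measures with a group factor exist.
- *That delivery weight goes uncollected.* Table 2 also has no row for cesarean delivery, induction, shoulder dystocia or admission to neonatal intensive care, all of which are listed outcomes. It is not a full list of delivery data, so the missing mark shows only that the source is not stated there.

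The objection does not remove two points. The sentence names a method that does not fit the outcome as defined, and on its most favourable reading it ignores a strong, known source of variation that is recorded for every woman.

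**Conclusion.** The point holds in a limited form. The stated method is at best a roundabout, unadjusted change-score test. Under the assumptions on entry, delivery and weekly gain above, it leaves variation with an SD of roughly 1.6 to 2.7 kg in the inclusion-to-delivery change that a baseline covariate could largely remove. This is noise unrelated to arm. The loss of later entrants and the absence of an arm comparison are conditional risks of a loosely worded sentence; the document commits to neither. The matter concerns one secondary outcome and does not touch the primary outcome or the sample size.

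**What to change.** Replace the sentence on weight in section 2.9 with a named between-arm analysis:

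- ANCOVA of weight at delivery, or the last weight before it, on arm, weight at inclusion and gestational age at inclusion. Using the change as the response gives the same arm estimate, because weight at inclusion is in the model.
- Alternatively, a linear mixed model of all available weights, with gestational age as continuous time and an arm-by-time term. This keeps women who have no 24-week visit.

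Use gestational age at the last weight only in a sensitivity analysis. It is measured after randomization and may itself be affected by treatment.

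State where the delivery weight comes from, for example the maternity record, and mark it in the Birth column of Table 2.

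The cost is a change of wording and, if delivery weight is not already collected, one abstracted value per woman. Both baseline covariates are already available.

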### Sample size

2.10

The sample size for the RCT was calculated as the number of participants needed to test the statistical significance of the difference between the two means (reduction in mean percent of BG readings exceeding target glycaemic levels from 15 to 11%, SD 10%) at a significance level of 0.05 and with a power of 0.80 for d/SD values = 0.4, including 25% dropout.

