**Methods:**

Women with GDM are randomized to 2 treatment groups: utilizing and not utilizing DiaCompanion I. The app provides women in the intervention group the resulting data-driven prognosis of 1-hour postprandial glucose level every time they input their meal data. Based on the predicted glucose level, they can adjust their current meal so that the predicted glucose level falls within the recommended range below 7 mmol/L. The app also provides reminders and recommendations on diet and lifestyle to the participants of the intervention group. All the participants are required to perform 6 blood glucose measurements a day. Capillary glucose values are retrieved from the glucose meter and if not available, from the woman’s diary. Additionally, data on glycaemic levels during the study and consumption of major macro- and micronutrients will be collected using the mobile app with electronic report forms in the intervention group. Women from the control group receive standard care without the mobile app. All participants are prescribed with insulin therapy if needed and modifications in their lifestyle. A total of 216 women will be recruited. The primary outcome is the percentage of postprandial capillary glucose values above target (>7.0 mmol/L). Secondary outcomes include the percentage of patients requiring insulin therapy during pregnancy, maternal and neonatal outcomes, glycaemic control using glycated hemoglobin (HbA1c), continuous glucose monitoring data and other blood glucose metrics, the number of patient visits to endocrinologists and acceptance/satisfaction of the two strategies assessed using a questionnaire.

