### Study design and setting

2.1

This study is an interventional open-labeled randomized controlled trial. A total of 216 women with GDM will take part in this trial performed in the Almazov National Medical Research Centre. Patients are randomized 1:1 to the intervention or control group. The intervention group receives DiaCompanion I app and standard antenatal care with the reduced number of visits to endocrinologists. The control group receives standard antenatal care. Patients participate in the study from recruitment (between 12 and 32 completed weeks of pregnancy) until delivery and will be invited to the follow-up visit at 3-6 months postpartum. The study protocol follows the Standard Protocol Items: Recommendations for Interventional Trials (SPIRIT) (11). Study design and data collection are shown in **Figure 1**. Please find the detailed information on the intervention and data collection in the sections below.

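### Read as a two-sided test, the sample-size inputs call for about 264–268 women with 25% dropout; the stated 216 allows for only about 7–8% loss, and sidedness is not stated

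*Protocol article*

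**What the plan says.** Section 2.10 (Sample size) describes a comparison of two means, with the effect given as "reduction in mean percent of BG readings exceeding target glycaemic levels from 15 to 11%, SD 10" percent and the standardised difference given "for d/SD values = 0.4". The error rates and the dropout allowance follow in the same sentence: "at a significance level of 0.05 and with a power of 0.80 for d/SD values = 0.4, including 25% dropout". That section prints no resulting number.

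The total appears in two other places. The abstract's Methods paragraph says "A total of 216 women will be recruited", and section 2.1 (Study design and setting) says "A total of 216 women with GDM will take part in this trial". Allocation is equal: "Patients are randomized 1:1 to the intervention or control group". Since the 216 are the women recruited, 216 is the number before dropout.

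On the test, section 2.9 (Data analysis) names Student's t-test, or the Mann-Whitney test where data are not normal, and says "The critical level of significance of the null statistical hypothesis will be assumed to be 0.05". Neither section says whether the test is one- or two-sided.

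**The concern.** The inputs and the total stand in different sections, and the article never shows the step from one to the other. With a standardised difference of 0.4, the usual two-sided calculation needs close to 100 women per arm before any dropout. A total of 216 is 108 per arm, which leaves little room for losing a quarter of them.

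The stated power is what readers will use to interpret the primary result, above all a null one. If the planned loss occurs and the test is two-sided, the chance of missing a true 4-point difference is about 28%, where section 2.10 implies 20%.

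**Working it through.** **Inputs**
- From section 2.10: difference 15 − 11 = 4 points; SD 10 points; d = 4/10 = 0.4, which agrees with the stated ratio; significance level 0.05; power 0.80; dropout 25%.
- From section 2.1: 216 women, 1:1, so 108 per arm.
- Assumption: two-sided test, because sidedness is not stated. One-sided is tried afterwards.

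**1. Can 216 be reproduced with a two-sided test?**

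Evaluable women per arm = 2(z₀.₉₇₅ + z₀.₈₀)²/d² = 2(1.960 + 0.842)²/0.4² = 98.1, rounded up to 99, so 198 in total. The exact t-test calculation gives 99.1, rounded up to 100, so 200 in total.

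| Dropout method | From 99 per arm | From 100 per arm |
|---|---|---|
| n/(1 − 0.25) | 132 per arm, 264 total | 134 per arm, 268 total |
| n × 1.25 (shortcut) | 124 per arm, 248 total | 125 per arm, 250 total |

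None of these is close to 216. If fractions are not rounded up at each step, the shortcut gives at least 196 × 1.25 = 245.

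**2. What loss does 216 cover on this reading?**

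1 − 198/216 = 8.3%; 1 − 200/216 = 7.4%.

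**3. What power remains if 25% give no primary-outcome data?**

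216 × 0.75 = 162, or 81 per arm. Normal approximation: 0.4 × √(81/2) = 2.546, and Φ(2.546 − 1.960) = 0.721. The t-test gives 0.716.

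Detectable difference with 80% power: (1.960 + 0.842) × √(2/81) × 10 = 4.4 points.

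Two-sided power by the share of women without data (normal approximation):

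| Loss | 0% | 5% | 8% | 10% | 15% | 20% | 25% |
|---|---|---|---|---|---|---|---|
| Power | 83.6% | 81.7% | 80.5% | 79.6% | 77.3% | 74.8% | 72.1% |

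With all 216 analysed, the t-test figure is 83.3%. If the Mann-Whitney test is used on near-normal data (relative efficiency 0.955), power at 162 women is about 70%.

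**4. Does a one-sided test explain 216?**

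Evaluable women per arm = 2(1.645 + 0.842)²/0.4² = 77.28, rounded up to 78. Then 78/0.75 = 104 per arm, 208 in total; the shortcut gives 196. Neither is 216.

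Power at 81 per arm is 81.6% (t-test 81.3%), so on this reading the shortfall disappears.

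One route reaches 216 exactly: 77.28/0.955 = 80.9, rounded up to 81; 81/0.75 = 108 per arm. It needs both a one-sided test and a Mann-Whitney inflation. It also depends on rounding: starting from 78 gives 78/0.955, rounded up to 82, then 82/0.75, rounded up to 110 per arm, or 220.

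**The case against.** The strongest reply is that the shortfall rests on a two-sided test, which the article never states. With a one-sided 0.05 test, 216 women more than cover 25% dropout, and there is a calculation that gives 216 exactly. A reader might infer that the stated inputs and the stated total cannot both be right; while sidedness is open, the article does not support so absolute a claim. What limits the reply is that section 2.10 describes a plain difference between two means and mentions neither a one-sided test nor a rank-test adjustment, and no directional hypothesis test is declared in section 2.9. Two-sided remains the conventional reading of the tests named there.

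The second reply concerns what dropout means. The primary outcome in section 2.8 is a percentage of readings accumulated from randomization to delivery, so a woman who leaves after some weeks may still contribute a value. Section 2.9 promises an intention-to-treat analysis of all randomized women, and the Discussion says that women who need insulin are followed until delivery. A reader might infer that the trial simply has 72% power; that holds only if every woman in the 25% gives no usable data. This reply reduces the likely size of the loss. It does not make 216 follow from the stated inputs, since an allowance of 25% should still be visible in the total.

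Two further inferences go too far. The total does hold some allowance, about 7–8% on the two-sided reading. And although 196 × 1.10 = 215.6 suggests that a 10% inflation was applied, that is a guess at the sponsor's working; the mismatch does not depend on it.

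**Conclusion.** The point stands in conditional form. Under a two-sided 0.05 comparison of means, 216 does not contain the 25% allowance that section 2.10 claims: about 264–268 would be needed, a gap of roughly 48–52 women. The consequence for power depends on how many women give no primary-outcome data: about 8 points below the stated 80% if the full 25% are lost, about 5 points at 20%, and no shortfall up to about 7–8%.

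The conclusion rests on two assumptions, two-sidedness and complete loss of outcome data among dropouts. If the calculation was one-sided, power is adequate at 81 per arm, but section 2.10 as written still does not lead to 216. On either reading the paragraph needs correction, because a reader cannot get from its inputs to the total.

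**What to change.** Correct section 2.10 and leave enrolment as it is.

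- State the sidedness and the test used for the calculation, including any rank-test inflation, and show the step from evaluable to recruited women.
- If the calculation was two-sided, state that 216 women give 80% power for a 4-point difference only with up to about 7–8% loss, and that with 25% loss (81 per arm) power is about 72% for 4 points, or 80% for 4.4 points.
- Say what counts as dropout for this purpose, that is, whether a woman with partial readings still contributes to the primary outcome.

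The cost is one paragraph of wording and, on the two-sided reading, a less favourable power statement. No additional women are required. Keeping both the 80% power and the 25% allowance under a two-sided test would instead mean recruiting about 264–268.
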